### **4. Administration of Surveys and/or Process:**

The online surveys will be collected in the Penn Medicine ED by trained research staff (clinical research assistants and/or Academic Associates). The eligibility surveys will take approximately 15 minutes to

complete via REDCap and the BLX survey website, and the baseline survey will take approximately 5-10 minutes to complete via Way To Health.

The Follow-Up survey will be accessed via text message and completed via Way To Health. The survey will take approximately 5-10 minutes to complete.

## **5. Data Management:**

All study personnel that will use this data are listed on the IRB application and have completed training in HIPAA standards and the CITI human subjects research. Computer-based files will only be made available to personnel involved in the study through the use of access privileges and passwords. Wherever feasible, identifiers will be removed from study-related information. Precautions are in place to ensure the data are secure by using passwords and encryption because the research involves web-based surveys. The use of paper-based records will be limited. Paper-based records will be secured in a locked cabinet in the principal investigator's office, retained for a maximum of 7 years after study completion and then destroyed.

## **7. Subject Follow-up:**

Participants will be contacted via text message to complete a brief survey via Way To Health of whether they were successfully enrolled in the benefits programs in which they had applied.

## **STUDY PROCEDURES:**

### **1. Detailed Description:**

Patients in Penn Medicine EDs will be recruited by trained clinical research personnel to participate in this two-arm prospective randomized controlled trial. Research personnel will pre-screen participants in the Electronic Health Record and confirm a positive likelihood of being discharged by the patient's clinical team (e.g., physicians or nurses). Research personnel will then approach participants, introduce the study, and ask the final pre-eligibility screening questions. Initially eligible and interested participants will provide electronic written informed consent and the BLX survey to confirm final eligibility. Participants must be eligible for at least one benefit for which BDT provides application assistance in order to continue in the study. Participants will then create an account in Way To Health and complete a baseline survey collecting information regarding sociodemographic characteristics, attitudes towards public benefits programs, and health-related social needs. All participants will receive \$20 via Greenphire VISA ClinCard for completing informed consent and the BLX survey.

Participants will then be randomized to either the control or intervention groups. Participants in the control arm will then receive the BenePhilly Summary Flyer providing the contact information to connect with a BDT enrollment navigator. Control group participants will also receive a one-time introductory text two hours after enrollment reminding them that they will be contacted via text message in 14 days to complete a follow-up survey. Patients randomized to the intervention arm will receive the BenePhilly Summary Flyer and an initial text message two hours after enrollment with instructions to expect follow-up texts one day post-discharge from the ED. At Day 1 post-discharge from the ED, patients will receive their first text message to connect with benefits enrollment navigators at BDT to apply for the benefits they may be potentially eligible to receive. On Day 3 post-discharge, participants will receive a text message assessing whether they have yet connected to BDT. If participants indicate that they have not yet connected with BDT on day 3, they will receive subsequent reminder text messages to connect with BDT on Days 7 and 14 post-discharge. After 14 days post-discharge, all participants will receive a patient satisfaction survey asking about their experience in the study. Text message schedules were adjusted to ensure that patients receive messages during business hours when BDT call center was operational.

Eligible study participants will also be consented to allow the study team to extract relevant clinical data from the EHR, including listed co-morbidities, prior ED and hospital utilization, access to primary care,

and payor type. We will extract these patient-level variables using Epic Clarity, an automated programming interface which permits secure queries of the electronic health record.

All survey data in Penn Medicine EDs will be collected via REDCap and Way To Health on designated secure, password-protected tablets. The BLX survey portion of the Eligibility Survey will be completed via secure BDT website prepared for this research study.

## **2. Data Collection:**

Survey data be collected using REDCap, Way To Health, and BDT. Data will also be collected via PennChart (EPIC) and patient self-report.

**3. Genetic Testing:** Not applicable

**4. Use of Deception:** Not applicable

## **STATISTICAL ANALYSIS PLAN**

### **1. Detailed Description:**

We will use descriptive statistics to summarize the data and patient characteristics. Baseline demographic and clinical characteristics will be reported as frequency and percent for categorical variables and median and distribution for continuous variables. We will compare baseline characteristics between intervention and control arms using t-tests for continuous variables and chi-squared tests for categorical variables. The goal of these comparisons will be to determine if the two arms are balanced on baseline variables after randomization.

Our primary analysis will focus on the difference in the number of phone calls received on the BDT phone line between the two arms. We will conduct an intent to treat (ITT) analysis. The ITT analysis will include all randomized participants in the groups to which they were randomly assigned. We will estimate and test differences in proportions between arms using two-sample z-tests. If necessary, multivariable logistic regression models that account for baseline measurements of patient demographic and clinical characteristics. Missing data will be assessed for patterns and multiple imputation will be used if deemed appropriate. A p-value of 0.05 will be deemed statistically significant but emphasis will be placed on point estimates and confidence intervals. Secondary outcomes including number of applications for public benefits submitted will also be compared using both unadjusted and adjusted models as described above.

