### 1. Target Population and Accrual:

The target population of this study includes patients presenting in Penn Medicine Emergency Departments (ED).

Target sample size: 188 patients

Pilot study: 30 patients

RCT: 158 patients

Power calculations were based on preliminary testing and a prior assumptions that a baseline rate of about 1% of patients would contact BDT after receiving a flyer at the time of discharge (control group), and 10% of patients would contact BDT after receiving text messages (intervention group). Based on these parameters, we estimate that a sample of 158 patients (79 per arm) would provide at least 80% power to detect a 9% difference between the two study arms, with one-sided statistical testing.

For practical reasons related to study funding and allocation of research staff, we may include one pre-specified interim analysis.

Alpha spending function using O'Brien Fleming efficacy boundary

For  $k = 2$

|     |        |        |
|-----|--------|--------|
| $P$ | 0.0088 | 0.0467 |
|-----|--------|--------|

|     |    |     |
|-----|----|-----|
| $N$ | 80 | 160 |
|-----|----|-----|

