## **Active Control Arm**

Participants in the control group will receive a summary flyer providing contact information for BDT, including the unique study phone line to connect with a BDT enrollment navigator. Currently, the standard of care is for ED patients to receive no information about public benefits. Therefore, the flyer represents an augmentation of usual care for patients randomized to the control group. Participants will also receive a one-time text message introduction to the study 2 hours after enrollment with a reminder that the study team will contact them in 14 days to complete a brief follow-up survey.

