### **No Interim Analysis**

Based on the literature and pilot work, we believe that the intervention (automated text messaging) can achieve a successful primary outcome (binary, whether or not a patient calls the benefits navigator) for 5-10% of study participants. We believe that the control group will achieve the same outcome 1% or less of the time. The minimum important difference that we believe is actionable for future interventions at scale is 5%. We elected to use one-sided testing given our primary interest in determining whether text messaging was more effective than paper flyers, which represented the standard of care. Given that this study had a limited funding and timing window, our power decisions also reflected practical considerations around study efficiency.

|                                        |             |
|----------------------------------------|-------------|
| Percentage success in treatment group: | 10%  |
| Percentage success in control group:   | 1%   |
| Alpha:                                 | 0.05 |
| Beta:                                  | 0.20 |

|                                |                  |
|--------------------------------|------------------|
| Ratio of treatment to control: | 1:1              |
| One-sided test                 |                  |
| Total sample size required     | 158 participants |

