### **Interim Analysis**

For practical reasons related to planning for study funding, timing of study completion, and allocation of research staff, we conducted one interim analysis. We did not specify specific stopping guidelines and planned to continue the study regardless of this interim analysis, but with potential changes in allocation of study personnel.

Alpha spending function using O'Brien Fleming efficacy boundary

|           |        |        |
|-----------|--------|--------|
| For k = 2 |        |        |
| P         | 0.0088 | 0.0467 |
| N         | 80     | 160    |

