### **Conclusion**

Our target study enrollment is 160 total patients, with one pre-specified interim analysis (without pre-determined stopping guidelines or plan for study cessation) at approximately 50% enrollment.

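### The protocol gives two final thresholds for the primary test, 0.05 and 0.0467, and does not say whether the interim look could support a claim of success

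*Protocol*

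**What the plan says.** Only the protocol is at hand, but it has its own Statistical Analysis Plan section, so the rule is fixed there and not left to another document.

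- **Analysis section (Statistical Analysis Plan, 1. Detailed Description).** "We will estimate and test differences in proportions between arms using two-sample z-tests", and then "A p-value of 0.05 will be deemed statistically significant but emphasis will be placed on point estimates and confidence intervals". It gives no side, does not say whether the variance is pooled, and does not mention an interim look.
- **Side.** Under No Interim Analysis: "We elected to use one-sided testing given our primary interest in determining whether text messaging was more effective than paper flyers". Target Population and Accrual and both Stata commands are also one-sided.
- **Boundary.** Target Population and Accrual and the Interim Analysis section both print a two-look table headed "Alpha spending function using O'Brien Fleming efficacy boundary": p = 0.0088 at N = 80 and 0.0467 at N = 160.
- **Status of the interim.** The Interim Analysis section reports the look as done and adds: "We did not specify specific stopping guidelines and planned to continue the study regardless of this interim analysis". Target Population and Accrual still describes it as something that may be included.
- **Size.** Target Population and Accrual says "RCT: 158 patients", and No Interim Analysis gives the same total. The Conclusion of the power section says "Our target study enrollment is 160 total patients, with one pre-specified interim analysis".

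**The concern.** The Conclusion adopts the design with an interim look. The final nominal level of that design is 0.0467, but the analysis section declares significance at 0.05, which is the level of the design without a look. An efficacy boundary exists to allow a claim at the interim, while the text around it says that nothing about the trial's course depends on the interim. No section says whether reaching 0.0088 would have counted as success, or which level governs the final test.

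An interim has been reported as done. While the threshold stays open, the rule could be settled after results are known, and a final p-value between 0.0467 and 0.05 could be called either way. The primary outcome is a rare binary event, so the z statistic takes few values, and one plausible outcome falls inside that narrow gap.

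**Working it through.** **Inputs.** Rates of 1% and 10%, one-sided alpha 0.05, power 80%, 1:1 allocation (No Interim Analysis). Looks at half and full information (Stata Commands). Boundary 0.0088 and 0.0467 (Interim Analysis). The 6% intervention rate is an illustration: 1% plus the stated minimum important difference of 5 points. It lies within the protocol's expected range of 5 to 10%.

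**1. Reproduce the 158.** Pooled two-proportion formula, no continuity correction:

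n per arm = [z(α)·√(2·p̄·q̄) + z(β)·√(p0·q0 + p1·q1)]² / (p1 − p0)²

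With p̄ = 0.055: [1.645·√0.10395 + 0.842·√0.0999]² / 0.09² = 78.3, so 79 per arm and 158 in total. This matches the protocol.

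**2. Reproduce the boundary and the 160.** For two equally spaced looks, the O'Brien-Fleming limits are c·√2 and c, with the two z statistics correlated √0.5. Setting the overall one-sided error to 0.05 gives c = 1.678 and limits of 2.373 and 1.678. The nominal one-sided p-values are 0.0088 and 0.0467, as printed. The sample size inflation is 1.0156: 78.3 × 1.0156 = 79.5, so 80 per arm and 160 in total.

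So 158 with 0.05, and 160 with 0.0088 then 0.0467, are each correct. They are the same overall one-sided 5% without and with a look. The conflict is that the protocol takes its size and interim from the second design and its stated significance level from the first.

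**3. Overall error under each reading** (1 − P(Z1 < b1, Z2 < b2), normal theory):

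| Rule | Overall one-sided error |
|---|---|
| Claim possible at 0.0088, then 0.0467 | 0.0500 |
| Claim possible at 0.0088, then 0.05 | 0.0532 |
| No claim possible at the interim, final at 0.05 | 0.0500 |

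These are large-sample figures. With 1% callers in both arms and 79 per arm, the exact size of the final pooled test taken alone is about 2.1% at 0.05 and 2.0% at 0.0467, because so few events are expected.

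**4. Data that split the two thresholds.** Take 1/79 against 5/79 callers, a difference of 4/79 = 5.1 points.

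- Pooled proportion: 6/158 = 0.0380
- Standard error: √(0.0380 × 0.9620 × 2/79) = 0.0304
- z = 0.0506/0.0304 = 1.665, one-sided p = 0.0480

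This passes 0.05 and fails 0.0467. At 80 per arm the p-value is also 0.0480.

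**5. How often this happens.** At 79 per arm with a 1% control rate, nearly all of the disagreement comes from that one table.

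- P(1 control caller) = 79 × 0.01 × 0.99^78 = 0.361
- P(5 intervention callers) = C(79,5) × p^5 × (1 − p)^74 = 0.0926 at p = 10% and 0.180 at p = 6%
- Products: 0.361 × 0.0926 = 3.3%, and 0.361 × 0.180 = 6.5%

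The full enumeration gives the same 3.3% and 6.5%.

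**6. Dependence on pooling.** With the unpooled standard error the same counts give p = 0.0465 (79 per arm) or 0.0466 (80 per arm), so both thresholds are passed. Unpooled tables that do split them, such as 7 against 14 (p = 0.0490), need far more control callers than a 1% rate produces. The disagreement is then essentially zero.

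**The case against.** The strongest reply is that there is one alpha here. One-sided 0.05 and 0.0467 sit under separate headings, without and with an interim. If the interim could never support a claim, testing at 0.05 at the end holds the error at 5%. The gap is 0.0033, its effect depends on an unstated choice of variance, and the protocol puts its emphasis on estimates and intervals. All of this stands, and it limits the size of the point. It does not say which level applies: the adopted design carries the boundary, and no section withdraws it.

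Four stronger readings are tempting and are not supported:

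- **A two-sided primary test.** The analysis section gives no side, so a reader might infer a two-sided 0.05 and a loss of power. No section says two-sided. Target Population and Accrual, No Interim Analysis and the Stata commands all say one-sided. The omission needs a word added and is not a rival rule.
- **An unblinded look.** A reader might infer that results by arm were seen at the interim. The protocol gives funding, timing and staffing as reasons and does not say who saw what.
- **A wrong boundary because of its label.** The table is headed as a spending function, but its figures are the classical O'Brien-Fleming limits and reproduce exactly. The label does not alter the rule.
- **An invalid reason for one-sided testing.** The flyer is called standard of care in the power section, whereas the control arm description says "Currently, the standard of care is for ED patients to receive no information about public benefits". The wording is inconsistent, but the flyer is the comparator either way and the success rule is unaffected.

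**Conclusion.** The concern holds in a limited form. The protocol states two final thresholds for one primary test, pairs an efficacy boundary with an interim that has no stated consequence, and carries two target sizes to match. If the interim could support a claim, 0.05 at the end is slightly too generous (5.3% overall). If it could not, 0.05 is valid and the boundary table does not belong in the plan. Either way one of the two statements must go.

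The practical effect is a different verdict in about 3% to 6.5% of trials. That assumes the pooled z-test, 79 per arm, a 1% control rate and intervention rates of 10% and 6%. With an unpooled test it is essentially nil. The 5.3% rests on normal theory with the look at exactly half the information. This should be fixed, because the primary decision rule ought to be unambiguous and the repair is cheap, but it does not threaten the design.

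**What to change.** Before final outcomes are linked to arm, write one rule and repeat it in Target Population and Accrual, Detailed Description, and all parts of the Power Analysis. Either version works:

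- **Keep the boundary.** One-sided pooled z-test, final success at p < 0.0467, target 160 (80 per arm). Say that an interim claim would have needed 0.0088. Report a confidence interval at the matching two-sided level, 1 − 2 × 0.0467 = 90.7%.
- **Drop the boundary.** State that the interim could support no efficacy claim, delete the boundary table in both places, and keep the one-sided pooled z-test at 0.05 with a 90% interval. Give one target size throughout.

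The first version costs a marginally stricter threshold and two patients whom the Conclusion already includes. The final test alone then has 79.8% power at 80 per arm, against 80.3% for one-sided 0.05 at 79 per arm (both normal approximation). The second costs only an amendment of wording, provided the sponsor can document that no claim was possible at the interim.

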### OBJECTIVES:

The objective of this randomized controlled trial is to test the effect of screening patients in Penn Medicine Emergency Departments for eligibility of public benefits programs and using text messages post-discharge to connect patients to benefits enrollment specialists at Benefits Data Trust (BDT). Eligible patients will be randomly selected to receive text messages for two weeks after Emergency Department discharge with the phone number to speak with a benefits enrollment specialist at BDT. The number of calls to the BDT phone line and the number of submitted applications to public benefits programs will be compared between patients receiving a summary flyer with the phone number for BDT and the text message intervention to connect with BDT in comparison to an active control group who receives only a summary flyer with the phone number for BDT.

**Primary outcome variable(s):** Participant connection to BDT measured by phone calls completed by confirmed participants to BDT.

**Secondary outcome variable(s):** Number of applications for public benefits programs submitted per participant by BDT.

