The focus of this proposal is to test whether patients identified in Penn Medicine Emergency Departments (ED) randomized to receive a warm handoff text messaging intervention are more likely to connect to study-specific BDT phone line and submit more applications for public benefits programs in comparison to patients who only receive a summary flyer with the BDT study-specific phone line upon discharge from the Emergency Department.

We propose to first survey patients to determine their eligibility for public benefits programs. Second, patients who are eligible for at least 1 of the 10 benefits programs to which BDT provides direct application support to complete applications will be randomly selected to either receive a flyer with the study-specific BDT phone number to apply for public benefits programs (active control) or receive a text messaging intervention for two weeks after leaving the ED with instructions to connect to the BDT study-specific phone line in addition to the flyer. Patients randomized to the intervention arm will receive an initial text message one day post-discharge from the ED with instructions for connecting with BDT and will receive subsequent reminders to connect with BDT on Days 3, 7, and 14 post-discharge. Patients who indicate that they have successfully connected with BDT on Day 3 will not receive intervention messages on Days 7 and 14. All patients, both those randomized to the control and intervention groups, will receive an end-of-study survey on Day 14 post-discharge from the ED to assess the patient's experience in the research study and provide a reminder about the number to connect with BDT.

Insights from this randomized controlled trial will inform future work evaluating benefits enrollment outcomes, the relationship between benefits enrollment and health care outcomes, and variations in health services use among patients connected to BDT in the ED.

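### The secondary outcome is a count of applications per participant, but the plan assigns it a z-test of proportions and logistic regression, neither of which analyses that count as it stands

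*Protocol*

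**What the plan says.** The Objectives name one secondary outcome: "Number of applications for public benefits programs submitted per participant by BDT". The Background frames the question as one of quantity, namely whether texted patients submit more applications than patients given only the flyer. Entry requires potential eligibility for one or more programmes ("patients who are eligible for at least 1 of the 10 benefits programs"), so a participant can file more than one application.

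Under Statistical Analysis Plan, 1. Detailed Description, two between-arm outcome methods are given. The unadjusted one is: "We will estimate and test differences in proportions between arms using two-sample z-tests". The adjusted one, to be used if necessary, is "multivariable logistic regression models that account for baseline measurements of patient demographic and clinical characteristics". The section then turns to the secondary outcome: "Secondary outcomes including number of applications for public benefits submitted will also be compared using both unadjusted and adjusted models as described above". A t-test appears in the same section, but only for comparing continuous baseline variables.

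On the error level, the section says "A p-value of 0.05 will be deemed statistically significant" without giving a side. The Power Analysis says "We elected to use one-sided testing".

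**The concern.** The outcome and the method do not match. A z-test of proportions needs a yes/no result for each participant, and so does ordinary logistic regression. The outcome as defined takes the values 0, 1, 2 and upwards. The protocol is not silent here, so this is not a detail left to a separate analysis plan: by explicit cross-reference it fixes methods that do not fit the outcome it defines.

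An analyst would have to add an unstated step, possibly after seeing the data. The choices are to dichotomise the count, to pool applications into a proportion, or to use a method the protocol does not name. These answer different questions and have different error rates. The outcome matters because it is the only secondary outcome and the one closest to the benefit the protocol claims, which is enrolment in benefit programmes.

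**Working it through.** **1. The protocol's own figure.** Inputs from the Power Analysis: 1% versus 10%, one-sided alpha 0.05, power 0.80, 1:1 allocation. With pooled variance under the null and no continuity correction:

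n per arm = [1.645·√(2·0.055·0.945) + 0.842·√(0.01·0.99 + 0.10·0.90)]² / 0.09² = (0.530 + 0.266)² / 0.0081 ≈ 78.3, rounded up to 79.

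The total is 158, as stated, with power 80.3% at 79 per arm. This concerns the binary primary outcome only. No figure is given for applications.

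**2. Does anything make the secondary outcome binary?** The Detailed Description also calls the primary outcome a number of calls and then tests proportions. The Power Analysis settles that case by stating that the primary outcome is whether or not a patient calls. No section says the same about applications.

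**3. What dichotomising costs.** Suppose 10% apply in each arm, with one application each under the flyer and three each under texting (illustrative). Applications per participant are 0.10 × 1 = 0.10 versus 0.10 × 3 = 0.30. The proportion with any application is 10% in both arms. The z-test and logistic model would see no difference although the defined outcome has tripled.

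**4. What pooling would cost.** Let a share p apply, with K applications each, and let m = p·E[K]. The true variance per participant is p·E[K²] − m². A proportion test on total applications over 79 assumes m(1 − m). Take p = 5% and K equally likely to be 1 to 4, so E[K] = 2.5 and E[K²] = 7.5:

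- m = 0.125
- true variance = 0.375 − 0.0156 = 0.359
- assumed variance = 0.125 × 0.875 = 0.109
- ratio = 3.29, so the standard error is too small by a factor of √3.29 = 1.81
- large-sample rejection rate = P(Z > 1.645/1.81) ≈ 0.18 instead of 0.05

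With K = 1 or 2 (E[K] = 1.5, E[K²] = 2.5) the ratio is 0.1194/0.0694 = 1.72, and rejection is about 0.105. With K = 1 the ratio is exactly 1 and there is no inflation.

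**5. Simulation under no true difference.** 79 per arm, 60,000 trials per setting, one-sided 0.05, with 3, 5, 5.5 and 10% applying. The documents give no application distribution, so K is an assumption. Ranges are over the four applying rates.

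| Applications per applicant | Any vs none | Pooled over 79 | Pooled over 790 (10 programmes each) | Difference in means, empirical variance |
|---|---|---|---|---|
| exactly 1 | 0.050–0.063 | 0.050–0.063 | 0.041–0.050 | 0.050–0.063 |
| 1–2 | 0.052–0.060 | 0.110–0.119 | 0.094–0.106 | 0.050–0.054 |
| 1–4 | 0.050–0.060 | 0.188–0.200 | 0.166–0.183 | 0.046–0.053 |

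**6. A wider set of assumptions.** Here 1 to 20% apply, with a mean of 1 to 3 applications each (one plus a Poisson count, capped at 10), and 40,000 trials per setting.

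- Any versus none: 0.020 to 0.057 one-sided, 0.007 to 0.053 two-sided. The low values come from the 1% rate.
- Means with empirical variance: 0.013 to 0.056 one-sided, 0.002 to 0.052 two-sided.
- Pooled over 10 programmes per participant, mean 1.5 to 3: 0.080 to 0.208 one-sided, 0.074 to 0.311 two-sided.
- Pooled in the same way, exactly one application each: 0.020 to 0.046 one-sided.

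The ceiling of 10 is also an assumption; the protocol does not state a maximum count.

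**The case against.** A reader might infer that the plan as written produces an invalid error rate for the secondary outcome. The documents do not support that. Inflation needs several applications from one person to be treated as independent units, and no section prescribes this. The intention-to-treat statement points the other way, since it makes the randomised participant the unit of analysis.

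The most natural way to carry the methods over is by analogy with the primary outcome: the proportion of participants with at least one application. That analysis has near-nominal error. This part of the objection stands, and it removes the charge of a likely false positive. It does not remove the mismatch, because the protocol declares only the primary outcome binary and any-versus-none does not measure applications per participant.

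A reader might also infer that logistic regression cannot be run on such data at all. That is too strong. A grouped-binomial form accepts a number of applications out of a known number of programmes, but it needs an allowance for overdispersion, and the protocol describes neither.

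The remaining objections concern weight. The outcome is secondary, the sample size and primary test do not rest on it, and the plan puts its emphasis on point estimates and confidence intervals. These are fair and lower the severity. The emphasis on estimates also strengthens the case for clarity, since a point estimate is useful only if it estimates the stated quantity.

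**Conclusion.** The concern holds in a limited form. A count per participant has been assigned methods for a yes/no outcome, and nothing in the protocol bridges the two. Under the likeliest reading (any versus none) the cost is a changed estimand and lost information, with one-sided error of about 0.05 to 0.06 at 3 to 10% applying. Only under pooling does the error rise: to about 0.11 with one or two applications per applicant, or 0.16 to 0.20 with one to four, and not materially if each applicant files one. These figures rest on assumed application distributions and on a procedure that the protocol does not prescribe, so they bound what the loose wording allows and do not describe what will happen.

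Severity: should be fixed. The result affects the interpretation of one secondary outcome and leaves the sample size and primary analysis untouched.

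**What to change.** Replace the last sentence of Statistical Analysis Plan, 1. Detailed Description with:

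> The number of applications per randomised participant (non-callers counted as zero) will be compared between arms as a difference in means, with a permutation test or a test using the empirical participant-level variance. The adjusted analysis will use a regression for the count with robust standard errors. The proportion of participants with at least one application will be reported as a supporting analysis, using the z-test and the logistic model.

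This matches the outcome in the Objectives, keeps all randomised participants and the promised adjusted analysis, and ranks the two summaries. It needs no new data, because Subject Privacy already has BDT returning, for each listed participant, whether they called and which benefits they applied for.

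The cost is one more analysis and a few lines of code. The interval will also be imprecise if very few control participants apply. At the assumed 1% control contact rate, the chance that none of 79 control participants calls is 0.99^79 ≈ 0.45, and without a call one would expect no BDT-submitted application. In that case a ratio from a count or logistic model has no finite estimate, which is a further reason to lead with the difference in means.
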